### **7.9.3 Safety Review Prior to Dose Escalation**

Following the 7 day period after immunization (and prior to a dose escalation) the LMM will review all available information regarding solicited and unsolicited AEs and SAEs. As there are 6 dose escalations (Doses 1b, 1c, 2b, 2c, 3b, and 3c), there will be 6 such reviews by the LMM. (See Section 8.1.2: ‘Vaccination Process’ and Appendix B [Section 17.2.5: ‘Specific Schedule of Events’]).

Dose escalation will not proceed until all of the following four events have occurred:

1. All study subjects in a given cohort (dose level) have received an injection of study vaccine, and
2. All such subjects have been followed for at least 7 days after the injection, and
3. The LMM has reviewed the available safety data (and has had the opportunity to discuss the data with the DSMB, if he feels it necessary), and recommends further dose escalation and
4. The PI has determined that none of the SAEs or dose limiting toxicities outlined in Section 7.9.2 have occurred.

An additional requirement obtains prior to the first two dose escalations (i.e., prior to Doses 1b and 1c, during the first month of injections). This is a requirement that the DSMB will also review the LMM safety data report (number 3 above) and must concur on the decision to dose escalate, and convey this directive to the PI in writing. For these first two dose escalations, therefore, concurrence to proceed must be forthcoming from both the LMM and the DSMB. Courtesy copies of these reports will also be sent to GSK Biologicals, MVI and SCI. The DSMB is not required to respond to data reports prior to subsequent dose escalations (Doses 2b, 2c, 3b or 3c), although it may do so at its own discretion.

### **7.9.4 Safety Review Prior to Administration of Consecutive Doses**

Reports from the PI to the LMM detailing all AEs and SAEs for the 7 day, post-dose observation period (as in Section 7.9.3), will also be provided to the DSMB, MVI, GSK Biologicals, and SCI following the administration of each of the three consecutive doses (i.e., the first report is due after the first doses [1/5 dose, ½ dose and full dose] have been administered, the second and third reports are provided after doses 2 and 3, respectively).

Administration of consecutive doses (Doses 1b, 1c, 2a, 2b, 2c, 3a, 3b, and 3c) will not proceed until all of the following four events have occurred:

1. All study subjects in a given cohort (dose level) have received an injection of study vaccine, and
2. All such subjects have been followed for at least 7 days after the injection, and
3. The LMM has reviewed the available safety data (and has had the opportunity to discuss the data with the DSMB, if he feels it necessary), and recommends further consecutive doses and
4. The PI has determined that none of the SAEs or dose limiting toxicities outlined in Section 7.9.2 have occurred.

The cumulative total of data safety reports to the LMM required per Sections 7.9.3 and 7.9.4, will be nine, one after each of the nine inoculations. These reports, and who will receive them, are summarized in Table 4.

**Table 4: Summary of 7-day post vaccination AE reports**

| Dose | Report must go to | | |
| --- | --- | --- | --- |
|  | LMM | DSMB | GSK, MVI, SCI |
| 1a | * | * | * |
| 1b | * | * | * |
| 1c | * | * | * |
| 2a | * |  |  |
| 2b | * |  |  |
| 2c | * | * | * |
| 3a | * |  |  |
| 3b | * |  |  |
| 3c | * | * | * |

NB: Upon review of all reports, the LMM must concur with the PI on proceeding with subsequent doses; The DSMB is required to concur only upon the reports for Doses 1a and 1b.

After the “Follow-up Period for Unsolicited AEs” (Day 120), a comprehensive Interim Safety Data Report will be compiled by SCI (See Sections 8.1.5 and 13.6) and submitted to the DSMB by early October 2003.

### **7.9.5 Procedures for Resumption of Dosing Following Discontinuation of Vaccination, Dose Escalation or Administration of Consecutive Doses**

Within 5 working days of discontinuation of further vaccinations, the DSMB Chairperson will convene a meeting (via teleconference, videoconference, face-to-face or a combination of these) to include the following 5 deliberating participants: the PI, the LMM, GSK Biologicals, MVI and the sponsor, to review and discuss the safety data and events leading to the vaccination discontinuation. (Other “observing” or consultative participants, e.g., SCI, USAID, etc, may also attend at the Chairperson’s pleasure.) At least 3 days prior to this meeting, the DSMB will disseminate copies of all relevant safety data to all meeting participants. The Chairperson of the DSMB will also chair this meeting.

There must be a unanimous decision by all meeting participants to re-start the vaccine administrations, either in all study subjects or in specific cohorts. If not, further vaccinations will not commence (again, either in all study subjects or in specific cohorts.) Meeting participants may request additional information prior to making a decision on re-starting or terminating vaccinations, in which case, the DSMB Chairperson will organize a subsequent meeting within 3 working days after the meeting participants have received the requested additional information.

The DSMB (or its designee)will produce and distributeminutes of any such meetings to participants within 5 working days and copies will be maintained at in the study site and with the study sponsor. In the event of either a re-start of vaccine administrations (after a temporary suspension) or a permanent vaccine discontinuation (in a cohort or in all study subjects), the PI will report this decision to all participating IRBs and ERCs within 5 working days.

The decision for *permanent discontinuation* of further vaccinations (in all study subjects or in specific cohorts) will take the final form of a formal recommendation by the DSMB to the sponsor (i.e., the Office of the Surgeon General, U.S. Army; POC: [name], USAMMDA, [name], USA).

### **7.9.6 Dose Discontinuation in Individual Subjects**

Reasons for discontinuation of study vaccine administration in an individual subject include, but are not limited to, the following:

1. Anaphylactic reaction following administration of study vaccine
2. Significant (Grade 3 or 4) reactions following administration of study vaccine (including severe pain, severe swelling, severe headache, persistent high fever or other severe systemic or local reactions) that, in the opinion of the investigator or sponsor, preclude further administration of study vaccine
3. The occurrence of an SAE (See Section 11.5.1) whose relationship to the study vaccine is judged to be possible or probable
4. Receipt of any investigative drug, investigative vaccine or immunosuppressive medication (inhaled or topical corticosteroids are allowed) within 28 days of study vaccine
5. The occurrence of other medical conditions, unrelated to study vaccine, which, in the opinion of the PI, contraindicate administration of study vaccine
6. Moderate or severe unsolicited AEs (clinical events or laboratory tests) that are indicative of new and significant end organ dysfunction

**Table 5: General Toxicity Table** (Modified from the Pediatric ACTG Toxicity Tables; See Ref. 43)

| **Event** | **Grade I** | | **Grade 2** | | **Grade 3** | | | **Grade 4** | |
| --- | --- | --- | --- | --- | --- | --- | --- | --- | --- |
| **Laboratory Values** | | | | | | | | | |
|  | Conventional  Units | SI Units | Conventional Units | SI Units | Conventional Units | SI Units | | Conventional Units | SI Units |
| Hemoglobin | 7.0-7.9 gm/dL | 4.4-4.9 mmol/L | 6.0-6.9 gm/dL | 3.8-4.39 mmol/L | <6.0 gm/dL | <3.8 mmol/L | | CHF 2o to anemia | CHF 2o to anemia |
| Leukocytes | 3.0-3.9 103  per mm3 | 3.0-3.9 109/L | 2.0-2.9 103  per mm3 | 2.9-2.0 109/L | 1.0-1.9 103  per mm3 | 1.9-1.0 109/L | | <1.0 103  per mm3 | <1.0 109/L |
| Platelets | 90,000-109,999 per mm3 | 90.0-109.9 109/L | 75,000-89,999  per mm3 | 75.0-89.9 109/L | 50,000-74,999 per mm3 | 50.0-74.9 109/L | | <50,000 per mm3 | <50.0 109/L |
| Creatinine | 1.1-1.9 mg/dL | 92-176 mol/L | 2.0-3.9 mg/dL | 177-353 mol/L | 4.0-5.9 mg/dL | 354-530 mol/L | | >6.0 mg/dL | >530 mol/L |
| ALT | 45-60 IU/l | 45-60 IU/l | 61-105 IU/l | 61-105 IU/l | 106-147 IU/l | 106-147 IU/l | | > 148 IU/l | > 148 IU/l |
| **Systemic Events** | | | | | | | | | |
| Fever | 37.5-38.0oC | | 38.1-39.0oC | | 39.1-40.5oC | | >40.5o persistent >48 hours | | |
| Loss of Appetite | Eating less than usual; No effect of normal activity | | Eating less than usual; Interferes with normal activity | | Not eating at all | | Not eating at all; Requires supplemental intake | | |
| Drowsiness | Drowsiness easily tolerated | | Drowsiness that interferes with normal activity | | Drowsiness that prevents normal activity | | Drowsiness eventuating in seizures or coma | | |
| Irritability/  fussiness | Crying more than usual; No effect on normal activity | | Crying more than usual; Interferes with normal activity | | Crying that cannot be comfort-ed; Prevents normal activity | | Irritability/fussiness eventuat-ing in seizures or coma | | |
|  |  | |  | |  | |  | | |
| **Local Events** | | | | | | | | | |
|  | | | | | | | | | |
| Injection site pain or necrosis | Minor reaction to touch | | Cries/protests on touch | | Cries when limb is moved; Spontaneously painful | | Necrosis at the site of injection (With or without pain) | | |
| Injection site swelling | < 5 mm | | 5-20 mm | | 21-35 mm | | > 35 mm | | |

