### **7.9.2 Criteria for Discontinuation of Vaccination**

If any of the following SAEs occur, discontinuation of vaccination will be invoked and the events will be reported as described in Section 11.5.

1. Death in any subject in which the cause of death is judged to be possibly, probably or definitely related to study vaccine
2. The occurrence in any subject of an anaphylactic reaction to study vaccine
3. The occurrence in any subject of a life-threatening SAE whose causal relationship to vaccination is judged to be probable or definite
4. The occurrence of one or more non-life-threatening SAEs whose causal relationship to vaccination is judged to be definite
5. The occurrence, in one or more subjects, of Grade 4 laboratory abnormalities (See Table 5, “General Toxicity Table”), judged to be probably or definitely related to receipt of study vaccine

The following dose limiting toxicities will preclude dose escalation to the next higher dose level or administration of consecutive doses within a dose level (See Table 5):

1. In 4 (10%) or more children within a cohort, occurrence of Grade 3 or greater solicited systemic (not local) AEs judged probably or definitely related to the study vaccine, , , or
2. In 4 (10%) or more children within a cohort, occurrence of Grade 2 or greater unsolicited AEs judged probably or definitely related to the study vaccine, or
3. In 4 (10%) or more children within a cohort, occurrence of laboratory studies indicating Grade 2 or greater toxicities that are judged to be probably or definitely related to the study vaccine.

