### **Solicited Adverse Events**

**Table 12. Solicited Adverse Event (AE) Categories**

| Categories | Adverse Events |
| --- | --- |
| Local (injection site) AEs | Pain at the injection site |
| Swelling at the injection site |
| General (systemic) AEs | Fever (i.e., axillary temperature  37.5°C) |
| Drowsiness |
| Loss of appetite |
| Irritability/fussiness |

N.B.: Axillary temperature will be recorded at the time of the clinic visit. Should additional temperature measurements be recorded at another time of day, the highest temperature will be recorded.

The assessment of severity/intensity will be as described in Section 11.2. For general signs and symptoms reported, the investigator should assign a causality as described in Section 11.3.

For all signs and symptoms reported, the investigator should report the outcome as described in Section 11.4.

**If an SAE (see Section 11.5) occurs at any time during the study period, the PI will inform the USAMRMC-RCQ within 24 hours by e-mail, fax or telephone and with a written report within 3 working days. The WRP/KEMRI Ethics Review Commit-tee, GSK Biologicals, HSRRB, MVI, the DSMB and the Local Medical Monitor will also receive the written report and so will also be notified within 3 working days.**

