## Assessment of Intensity

Intensity of solicited AEs will be assessed and graded by the investigator as presented in Table 13.

| **Table 13. Assessment of Solicited Adverse Event (AE) Intensity** | | |
| --- | --- | --- |
| **AE** | **Grade** | **Intensity Definition** |
| Pain at injection site | 0 | Absent |
|  | 1 | Minor reaction to touch |
|  | 2 | Cries/protests on touch |
|  | 3 | Cries when limb is moved/spontaneously painful |
| Swelling at injection site | 0 | Absent |
|  | 1 | < 5 mm |
|  | 2 | 5-20 mm |
|  | 3 | > 20 mm |
| Fever | 0 | < 37.5°C |
|  | 1 | 37.5-38.0°C |
|  | 2 | 38.1-39.0°C |
|  | 3 | > 39.0°C |
| Irritability/Fussiness | 0 | Behavior as usual |
|  | 1 | Crying more than usual/ no effect on normal activity |
|  | 2 | Crying more than usual/ interferes with normal activity |
|  | 3 | Crying that cannot be comforted/ prevents normal activity |
| Drowsiness | 0 | Behavior as usual |
|  | 1 | Drowsiness easily tolerated |
|  | 2 | Drowsiness that interferes with normal activity |
|  | 3 | Drowsiness that prevents normal activity |
| Loss of appetite | 0 | Normal |
|  | 1 | Eating less than usual/ no effect on normal activity |
|  | 2 | Eating less than usual/ interferes with normal activity |
|  | 3 | Not eating at all |

NB: These intensity grades for solicited AEs are consistent with the intensity grades for the same events presented “Table 5: General Toxicity Table”, except that in Table 5 the grade 3 intensities (for all 6 events) are further divided into grade 3 and 4 intensities.

For each solicited symptom, the subject’s parent(s) will be asked if medical advice was sought (i.e. contact attempted with medical personnel) for this symptom.

For all other AEs, maximum intensity should be assigned to one of the following categories:

0 = No adverse event

1 = An adverse event that is easily tolerated by the subject, causing minimal discomfort and not interfering with everyday activities.

2 = An adverse event that is sufficiently discomforting to interfere with normal everyday activities.

3 = An adverse event that prevents normal, everyday activities. (Such an adverse event would, for example, prevent attendance at school, church or other typical assemblies, and would necessitate the administration of corrective therapy.)

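### The Table 5 fever row gives no grade to a fever above 40.5°C lasting 48 hours or less, so the dose-limiting count in Section 7.9.2 can miss such a fever if that table is applied literally

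*Protocol*

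**What the plan says.** Three places in the protocol bear on how a fever enters the dose-limiting count.

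- **Section 7.9.2** sets the rule: "In 4 (10%) or more children within a cohort, occurrence of Grade 3 or greater solicited systemic (not local) AEs" that are judged probably or definitely related. Meeting it "will preclude dose escalation to the next higher dose level or administration of consecutive doses within a dose level (See Table 5"). The table cited is Table 5; Table 13 is not mentioned.
- **Section 7.9.6, Table 5** has a fever row with Grade 1 at 37.5 to 38.0°C, Grade 2 at 38.1 to 39.0°C, Grade 3 at 39.1 to 40.5°C and Grade 4 at ">40.5o persistent >48 hours".
- **Section 11.2** says "Intensity of solicited AEs will be assessed and graded by the investigator as presented in Table 13". There, Grade 3 fever is anything above 39.0°C, with no ceiling and no duration condition. The note under the table calls the two gradings consistent, "except that in Table 5 the grade 3 intensities (for all 6 events) are further divided into grade 3 and 4 intensities".

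Fever is one of the four solicited systemic events (Table 12, Section 11.1.5). Where more than one temperature is taken in a day, "the highest temperature will be recorded".

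**The concern.** If Table 5 only subdivides Grade 3 of Table 13, then its Grades 3 and 4 together must cover everything above 39.0°C. In the fever row they do not, because Grade 3 is capped at 40.5°C while Grade 4 needs both a higher temperature and persistence. The hotter but shorter fever falls between the two cells.

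Within the table that the rule cites, the grading is then not monotone: a fever of 40.2°C counts and a brief one of 40.8°C does not. The count is a gate. Sections 7.9.3 and 7.9.4 make each escalation and each consecutive dose conditional on the investigator finding that no dose-limiting toxicity of Section 7.9.2 has occurred. With a threshold of 4 children, a single child can decide it. The solicited-event tables, graded by Table 13, could also disagree with the safety decision about the same child.

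**Working it through.** The protocol gives no figure to reproduce here. The check applies both fever rows to the same temperatures, read to one decimal.

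| Peak axillary temperature | Table 13 | Table 5, 48 h or less | Table 5, more than 48 h |
|---|---|---|---|
| 39.0°C | 2 | 2 | 2 |
| 39.1°C | 3 | 3 | 3 |
| 40.5°C | 3 | 3 | 3 |
| 40.6°C | 3 | none | 4 |
| 41.0°C | 3 | none | 4 |
| 41.5°C | 3 | none | 4 |

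The two rows agree up to 40.5°C. Above it, a long fever behaves as the note describes (Grade 3 becomes Grade 4), and a short one has no grade in Table 5.

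**Other solicited events.** Fever is the only row with this gap. Swelling has a capped Grade 3 (21 to 35 mm), but Grade 4 starts where it ends (above 35 mm). For loss of appetite, Grade 4 adds a condition to a Grade 3 that has no cap, so nothing falls out. Only fever combines a capped Grade 3 with an extra condition on Grade 4.

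**Effect on the count.** Take a cohort with three children whose related fevers peak within 39.1 to 40.5°C, and a fourth with a related 40.8°C on Day 1 and 37.0°C on Day 2.

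- Table 5 alone: 3 + 0 = 3, below 4, rule not met.
- Table 13 and its note: 3 + 1 = 4, rule met.

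The fourth child is missed only if nothing else brings the child in: no other daily record between 39.1 and 40.5°C, and no other related solicited systemic event of Grade 3 or more.

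**Illustration of size.** The documents give no rate for such fevers, so these inputs are assumptions. Let n be the children counted, p the chance that a child has a related solicited systemic event of Grade 3 or more, and s the share of those children left uncounted. The chance of meeting the rule is P(X ≥ 4) with X ~ Binomial(n, p(1 − s)).

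| n | p | s = 0 | s = 5% | s = 10% | s = 20% |
|---|---|---|---|---|---|
| 45 (whole cohort) | 0.05 | 0.187 | 0.164 | 0.143 | 0.105 |
| 45 | 0.10 | 0.671 | 0.630 | 0.586 | 0.490 |
| 45 | 0.15 | 0.922 | 0.900 | 0.874 | 0.805 |
| 45 | 0.20 | 0.987 | 0.981 | 0.972 | 0.944 |
| 30 (FMP-1 recipients) | 0.05 | 0.061 | 0.052 | 0.044 | 0.031 |
| 30 | 0.10 | 0.353 | 0.317 | 0.283 | 0.216 |
| 30 | 0.15 | 0.678 | 0.636 | 0.591 | 0.493 |
| 30 | 0.20 | 0.877 | 0.848 | 0.814 | 0.730 |

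With 5% uncounted, the loss is at most 0.042 (0.678 − 0.636). With 20% uncounted, it reaches 0.185 (0.678 − 0.493). All of it presumes that Table 5 is applied literally and alone.

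**The case against.** The strongest reply is that the protocol already shows what it means. Investigators grade solicited fever by Table 13, the note says that Table 5 merely divides Table 13's Grade 3, and the trigger is Grade 3 or greater, so the side of the split does not matter. On that reading a one-day fever of 40.8°C counts. This stands as evidence of intent. It does not remove the conflict: the rule names Table 5, no sentence says that Table 13 overrides it for the count, and the note relied on is itself inexact for fever.

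A second reply is that the count is not the only safeguard. The local medical monitor reviews the data after each of the nine inoculations and must recommend proceeding, and the DSMB must also concur before doses 1b and 1c. The temperature would be in front of them whatever its grade. This also stands, and it limits the consequence.

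A reader might infer three stronger things, none of which the documents support:

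- **That the hottest fevers are in fact dropped from the count.** They can be if Table 5 is read literally. Under Table 13 and its note they are not.
- **That the gap changes who is individually taken off vaccination.** The list in Section 7.9.6 is expressly not exhaustive, and its item on Grade 3 or 4 reactions turns on the opinion of the investigator or sponsor. A missing grade neither forces nor prevents that decision.
- **That a fever above 40.5°C lasting three days escapes because it has no grade in its first 48 hours.** The reviews follow at least 7 days of follow-up (Sections 7.9.3 and 7.9.4), with reports 8 days after each dose (Section 11.1.4). A three-day fever starting soon after vaccination would be Grade 4 by then.

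**Conclusion.** The concern holds as an internal inconsistency in a decision rule. The Table 5 fever row leaves one region ungraded: above 40.5°C for 48 hours or less. This contradicts the stated relation between the two tables, and it sits in the table that the dose-limiting rule cites. The possible effect is an undercount, by one for each affected child, against a threshold of 4.

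The practical size is probably small. The fever must be very high, short, judged probably or definitely related, and the child's only qualifying event, and the review by the monitor (and by the DSMB at the first two escalations) remains. That such fevers are few is a judgement, since the protocol gives no rate. The point is worth settling because a rule that gates escalation and further dosing should not depend on its users repairing the grading table for themselves.

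**What to change.** Reconcile Section 7.9.2, the fever row of Table 5 in Section 7.9.6, and Table 13 with its note in Section 11.2, so that:

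- the two fever gradings agree with the relation that the note states, or the note is changed to describe the relation that holds;
- no combination of temperature and duration is left without a grade;
- it is clear which grading the Section 7.9.2 count uses, given that the rule cites Table 5 while investigators grade solicited events by Table 13.

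Which grade the short, very high fever should carry is the sponsor's clinical decision, and none is proposed here. The cost is about one table cell and one cross-reference, with no change to sample size, visits or data collected.

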### **7.9.7 Safety Precautions for Study Personnel**

Laboratory safety and blood-borne precautions for all USAMRU-K laboratories are delineated in the following USAMRU-K SOPs:

1. Lab Safety SOP #1: “Blood-borne and Infectious Control SOP”
2. Lab Safety SOP #2: “Hazard Communication and Chemical Hygiene SOP”
3. Lab Safety SOP #1: “Laboratory Safety SOP”
4. Phlebotomy SOP #1: “Phlebotomy Training and Emergency SOP”
5. Phlebotomy SOP #2: “Finger-stick SOP”

# CONDUCT OF THE STUDY

## General Study Aspects

### Screening and enrollment process

(See also SSP No. SM-01: Recruitment & Informed Consent Process, and SSP No. SM-02: Screening Day Procedures.)

Recruitment and screening will be incremental until the desired number of subjects are enrolled. Non-coercive means of recruitment will be used according to existing U.S. Army regulations (viz., AR 70-25 and AR 40-38). Community leaders (assistant chiefs and local village elders) will be formally briefed in their own language on the nature and purpose of the study. They will be allowed to freely ask questions of the PI. Parents of prospective subjects will view a videotaped briefing on the nature and purpose of the study and will then receive both oral and written explanations of the study, after which written informed consent will be obtained from at least one parent per subject. No questions relating to health will be asked of parents or children prior to consenting. So that illiteracy will be no bar to informed consent, all such briefings and explanations will be in the parents’ own language. All screening tests (see below) will be performed after only parental informed consent has been obtained.

A source documentfile will be prepared by the investigator at screening. These forms will be labeled with the subject's initials and a subject identification (SID) number, and will contain information about the subject's date of birth and medical history, date of screening visit, whether the subject was enrolled or not and (where applicable) reasons for exclusion from the study.

Parents of subjects will provide a medical history (with special attention to any history of recurrent infections to suggest immune suppression, previous history of splenectomy, and prior vaccine reactions). Subjects will also undergo physical examination and routine standard laboratory screening tests, which include complete blood count (CBC) and serum chemistry profiles (creatinine, ALT). Subjects will be excluded from participation if they meet any of the exclusion criteria (Section 7.5). Subjects excluded from this study because of significant abnormalities will be referred to the local health center for evaluation. All screening tests will be completed within 35 days prior to entry into the study; laboratory tests may be conducted at other times during the course of the trial if judged necessary for the safety of the subject by the investigators. All subjects randomized into the study will be identified and followed by SID number and by name (full name in source documents, but no name or initials in CRFs). All screening and follow-up diagnostic laboratory studies will be performed at the WRP Kombewa Clinic laboratory. Information gathered during screening (medical history, physical examination, and laboratory analysis) will be recorded in the screening source documents.

The investigator will ensure randomization (See also Section 10.3) of 135 eligible subjects who fulfill all the inclusion criteria and none of the exclusion criteria. Subjects in each cohort will be randomized separately from the other cohorts, at the times of first vaccinations. A picture ID of parent and child will be created and given to each parent. Copies of these pictures will also be kept in the source document file. A Case Report Form (CRF) will be filled in for all subjects enrolled in the study. All data collected during the study will be recorded on source documents and transcribed into the CRF by a transcription team trained in this process.

